**Review quality instrument version 4**

An established validated review quality instrument consisting of seven items formulated as questions that relate to importance of the research question, originality, method, presentation, constructiveness of the comments, substantiation of comments and interpretation of results is used. Each of the seven items scores in a five-point Likert scale from 1 (=poor) to 5 (=excellent). An additional eighth question assessed the overall tone of the review ranging from abusive to courteous. A total score is based on the mean of the eight items scores.17 (Figure 1)

**Outcome assessment**

- **Main outcome**
  - Quality of referee reports (based on the used review quality instrument)
- **Secondary outcomes:**
  - Participation rate, i.e. number of reviews and/or author comments per paper in open peer review
  - **Quality of referee reports (based on the BJS scoring system for peer review quality)**
  - **Reviewer’s recommendation regarding publication (**accept paper without changes needed, publish with major revision, publish with minor revision, reject.)

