**Standard peer review process**

In the standard process, the manuscripts are subject to external reviewing only. The handling editor sends the paper to two to four referees of his/her choice. The referees are asked to return their reports to the editorial office within two weeks. Referees use the current online evaluation forms. After submission of at least two referee reports, the handling editor scores the reports according to standard BJS policy and according to the existing specific review quality instrument as described below.

Eventually, the handling editor makes a decision: accept paper without changes needed, invitation to resubmit the paper following major or minor revisions or rejection of the manuscript. This review process takes on average 22 days. By default, the open peer review is single-blinded in which the reviewer’s name is not disclosed to the authors.

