**Open peer review through online system**

Following submission a manuscript will simultaneously go through standard peer review and also to the innovative process under study.

At the same time, the manuscript will be posted on a dedicated website for open access reviewing using Google Docs.

A mail is sent out every fortnight inviting potential referees as outlined below to review posted papers Abstracts of posted papers are included in this mail as well as a direct link to the paper and the online website. The email also contains an unsubscribe link.

Referees who like to review the paper on the open website are asked to adhere to the same online evaluation forms (standard referee sheet) as in the standard peer review process. It is also mentioned that the handling editor makes the final decision and that the reviewers should not mention in their reports whether the manuscript merits publication or not.

Once the review has been submitted, it will be immediately posted on the website and will be accessible to authors and other invited reviewers, i.e. open. By default, reviewers’ names and affiliations will be shown; anonymous reviewing is not allowed. Authors are notified via e-mail when a new review is posted.

After a period of 21 days, the manuscript and corresponding referee reports will be removed from the website and stored at manuscript central?).

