**Study time frame**

Consecutive papers are included within a predefined timeframe.

- - Start date: 1^st^ April 2015
  - End date: 31^st^ May 2015

This will yield approximately 170 papers (taking into account that roughly 150 papers are submitted to BJS each month, that roughly n=25 papers per month are rejected outright without undergoing formal peer review and that roughly 70% of authors will provide informed consent for the study).

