**Data management and analysis**

The quality of the referee reports between the two different review processes (standard *versus* open) will be compared using non-parametric statistics.

Number of open reviews per paper and number of comments per paper will be calculated.

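### Reviewers' publication recommendation is a secondary outcome, but open reviewers are told not to say whether a paper merits publication, and no other way of collecting it is described

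*Combined protocol and SAP*

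**What the plan says.** Under Outcome assessment, the third secondary outcome is the reviewer's recommendation regarding publication, in four categories: "accept paper without changes needed, publish with major revision, publish with minor revision, reject". The entry does not say whether it covers standard referees, open reviewers or both.

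Under Open peer review through online system, open reviewers are told that the handling editor decides and that "the reviewers should not mention in their reports whether the manuscript merits publication or not". The same section says that they "are asked to adhere to the same online evaluation forms (standard referee sheet) as in the standard peer review process". Once submitted, the open review is made public to the participants: "it will be immediately posted on the website and will be accessible to authors and other invited reviewers". Reviews are signed.

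Under Standard peer review process, the only statement on the form is "Referees use the current online evaluation forms". There is no ban on giving a recommendation. The fields of the form are not listed in either section.

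Under Data management and analysis, the between-process comparison is of one thing: "The quality of the referee reports between the two different review processes". Counts of open reviews and comments per paper are also planned. Recommendations are not mentioned.

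**The concern.** A choice among accept, revise or reject is a statement about whether a paper merits publication. The protocol therefore names an outcome that one of its two processes is told to withhold, and describes no other route by which that process could supply it.

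At stake is whether the study can say anything about how open reviewers' recommendations relate to those of invited referees. Every included paper passes through both processes, so the within-paper contrast is the natural use of this outcome. If open-side recommendations exist only where reviewers ignored the instruction, that subset is self-selected and cannot be assumed representative. The missing recommendations cannot be reconstructed once the reviews are in. The study is also meant to prepare a larger randomised trial, which could inherit the same gap.

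**Working it through.** **1. The plan's own figure.** Study time frame gives roughly 150 submissions per month, roughly 25 rejected outright per month, roughly 70% consent, and inclusion from 1 April to 31 May 2015, which is 2 months.

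- Expected papers = (150 - 25) x 2 x 0.70 = 175.
- The plan states approximately 170. The difference is 5/170 = 2.9%, so the figure reproduces within rounding. I use 170 below.

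**2. Standard-side recommendations.** Standard peer review process has the editor act after at least two reports.

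- Minimum = 170 x 2 = 340 (with 175 papers, 350).
- This assumes that every included paper reaches two reports and that each report carries a recommendation.

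**3. Open-side recommendations.** No number of open reviews per paper is assumed in the plan, so no expected total can be computed. What the text implies about content can be worked through by cases, because the form is not shown:

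| Standard referee sheet | Open reviewer follows the instruction | Open reviewer does not |
|---|---|---|
| No separate recommendation item | No recommendation | Recommendation in the posted text, from non-compliers only |
| Separate item, posted with the review | Item left blank, or the posted review shows what the instruction meant to keep out | Recommendation posted |
| Separate item, not posted | Recommendation available | Recommendation available |

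Only the last row gives usable open-side data from all reviewers, and the protocol nowhere describes it. The text says "Once the review has been submitted, it will be immediately posted on the website" without exempting any part of the form. Open review also runs on a separate site built on Google Docs, so a field in the journal's own system would not necessarily carry over to it.

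**4. Other places that might supply the outcome.** Final decision describes scoring the quality of open reports, but no step that collects or extracts a recommendation. Data management and analysis covers report quality and counts only. I found no section that reconciles the instruction with the outcome.

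**The case against.** The strongest reply is that the instruction covers only what reviewers mention in their reports, while open reviewers use the same sheet as standard referees. Four fixed categories look like a tick-box item, and such an item could sit outside the report text. The protocol says that the review is posted, not that every form field is displayed. This stands as a possibility. A reader might infer that the recommendation cannot be compared at all, or that any recommendation box must be posted. The documents do not support either, because the sheet is not reproduced. They show only that no collection route is stated and that the one relevant instruction points the other way.

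A second reply is that no comparison of recommendations is promised. That is also correct: neither Outcome assessment nor Data management and analysis says standard versus open for this outcome, and none of the listed aims concerns differences in recommendations. The comparison is an inference from the two-process design. On the text, the outcome might have been meant for standard referees only. But then the outcome lacks a stated population as well as an analysis, and the protocol still needs a sentence to say so.

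On size, a reader might multiply 170 papers by four referees and quote 680 standard recommendations as the upper end. That needs four invitations per paper and every report returned, which the plan does not claim. Only the minimum of about 340 follows.

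Finally, the main outcome, the participation rate and the journal's own quality score are untouched, and the editor decides blinded to open comments. This stands, and it limits the severity.

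**Conclusion.** The concern holds in conditional form. As written, and unless the standard referee sheet has a separate recommendation item kept out of the posted report, compliant open reviewers provide no recommendation. Any open-side recommendations would then come from reviewers who did not follow the instruction. The imbalance is at least about 340 standard recommendations against none under full compliance. With partial compliance the open-side number is unknown, and the direction and size of any selection bias cannot be derived from the documents. Separately, and whatever the form contains, no analysis is specified for this outcome.

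The severity is moderate. One secondary outcome of an observational feasibility study is affected; the main outcome is not. It should be settled before the first paper is posted, because the data cannot be recovered later.

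**What to change.** - **Open peer review through online system:** keep the ban in the posted text. Add that each open reviewer also gives the four-category recommendation in a structured field, stored for the study team and not posted. If the standard sheet already has such an item, one sentence saying that it is completed by open reviewers and withheld from posting is enough.
- **Outcome assessment:** state that the outcome is collected from both standard referees and open reviewers.
- **Data management and analysis:** add a within-paper comparison among papers with at least one recommendation from each process. A simple non-parametric or agreement analysis suffices, for example a signed-rank test on per-paper median categories, or a tabulation of agreement. The category order should be stated, since the current list places major before minor revision. A more elaborate ordinal model is a matter of preference.
- **Fallback:** if a non-posted field is not feasible, restrict the outcome to standard referees or delete it.

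The cost is one extra item on the open form and a few sentences of text, with no additional papers. The documents do not say whether the Google Docs-based site can hold a field that is not displayed. This could be checked in the ten-paper pilot planned for March; the fallback applies if it cannot.

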**Study time frame**

Consecutive papers are included within a predefined timeframe.

- - Start date: 1^st^ April 2015
  - End date: 31^st^ May 2015

This will yield approximately 170 papers (taking into account that roughly 150 papers are submitted to BJS each month, that roughly n=25 papers per month are rejected outright without undergoing formal peer review and that roughly 70% of authors will provide informed consent for the study).

**Costs**

By using Google Docs, which is free of charge only minimal costs will be incurred. If any unforeseen costs are encountered, a timely notification should be sent to [name], chief editor of BJS.

**Data management and analysis**

The quality of the referee reports between the two different review processes (standard *versus* open) will be compared using non-parametric statistics.

Number of open reviews per paper and number of comments per paper will be calculated.

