**Study design**

An observational feasibility trial. Included papers will undergo conventional peer review and simultaneous open peer review.

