**Final decision**

The responsible editor handles the manuscript in a standard way; he/she makes a decision, based on the standard peer review blinded to the comments from the open peer review process. Once the final decision is made, he/she then evaluates the online open referee reports according to standard BJS policy. The referee reports from the open review process are available to the author and can be used to improve the paper when resubmission is requested (first revision, i.e. R1) or for submission to another journal.

The assistant editors however, score all referee reports (invited reports and those from the open review process) according to the review quality instrument as described below. The assessors are not blinded to the source of the referee reports (invited *versus* open).

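### The main comparison names no test or unit of analysis and makes no use of the within-paper pairing, so a report-level reading could show differences in paper mix as differences in review quality

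*Combined protocol and SAP*

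**What the plan says.** All places are in the combined protocol and SAP.

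- Study design: "Included papers will undergo conventional peer review and simultaneous open peer review". Each paper is therefore its own control.
- Standard peer review process: "The handling editor sends the paper to two to four referees of his/her choice". Scoring follows "After submission of at least two referee reports", so the standard side has at least two reports per paper.
- Open peer review through online system: open referees choose what to review ("Referees who like to review the paper on the open website are asked to adhere to the same online evaluation forms").
- Outcome assessment: the open count is itself a secondary outcome ("Participation rate, i.e. number of reviews and/or author comments per paper in open peer review"), and nothing guarantees that it exceeds zero. The main outcome is "Quality of referee reports (based on the used review quality instrument").
- Final decision: the assistant editors "score all referee reports (invited reports and those from the open review process"), so the raw data are one score per report.
- Data management and analysis: quality under the two processes "will be compared using non-parametric statistics". That section gives no named test, unit of analysis, pairing or clustering rule, effect estimate, interval or significance level.

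**The concern.** The design supplies matched data, but the analysis sentence takes the referee reports of the two processes as the things compared and does not mention the paper. Two analyses that both fit the sentence can disagree on the same data: a Mann-Whitney test on all reports, and a signed-rank test on paper-level differences.

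The report-level version has two weaknesses. First, reports on the same paper may be correlated, and the test ignores this. Second, a paper with no open report contributes to the standard side only, while a paper that attracts many volunteers is over-represented on the open side. If the papers that attract volunteers also tend to draw higher- or lower-scoring reports, the comparison is biased, and a larger sample does not remove the bias. Pairing removes any effect that a paper has on both sides equally.

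At stake is the interpretation of the main outcome of a study meant to prepare a randomised trial.

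**Working it through.** **Plan's own figure.** Study time frame gives 150 submissions and 25 outright rejections a month, two months and 70% consent: (150 − 25) × 2 × 0.70 = 175, against about 170 stated. This agrees within 3%. I use 170 papers.

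**Inputs.** From the documents: 170 papers and 2–4 standard reports each (taken as equally likely, mean 3). Assumed, because the documents are silent: a mean of one open report per paper (three in the balanced case), the spread of those counts, the intraclass correlation (ICC) of scores within paper, and two-sided 5%.

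**Papers with both report types.** With Poisson counts of mean 1, 170 × (1 − e⁻¹) = 107. With negative binomial counts of mean 1 and dispersion k, the chance of no open report is (k/(k+1))^k. This leaves 72, 61 and 51 papers for k = 0.5, 0.3 and 0.2.

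**Pooling when open counts are unrelated to the paper.** Let paper i have s_i standard and o_i open reports, with totals S and O, and let total variance be 1. The variance of the difference in pooled means is

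ICC × A + (1 − ICC) × h, where A = Σ(o_i/O − s_i/S)² and h = 1/O + 1/S.

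A test that treats reports as independent assumes h. With ratio r = (true variance)/h, its type I error is about 2[1 − Φ(1.96/√r)].

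Worked case, k = 0.3 and ICC 0.3:
- O = 170 and S = 510, so h = 0.00784.
- The expected square of o_i is 1 + 1/0.3 + 1 = 5.33, and that of s_i is 9.67.
- A = 5.33/170 + 170 × 9.67/510² − 2/170 = 0.0259.
- r = (0.3 × 0.0259 + 0.7 × 0.00784)/0.00784 = 1.69, which gives an error of 13%.

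Simulation with no true difference (3000 runs per setting for the rows marked *, 1000–1500 otherwise):

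| Open counts | ICC | Formula | Pooled Mann-Whitney, simulated |
|---|---|---|---|
| Balanced, 2–4* | 0.1 / 0.3 / 0.5 | 4.1 / 2.5 / 1.2% | 4.4 / 2.1 / 1.3% |
| Poisson, mean 1 | 0.22 | 4.5% | 4.7% |
| Skewed, k = 0.5 | 0.05 / 0.10 | 5.8 / 6.5% | 4.7 / 6.0% |
| Skewed, k = 0.5 | 0.22 | 8.4% | 7.3–9.5% |
| Skewed, k = 0.2 | 0.22 | 14.1% | 12.5–14.4% |
| Skewed, k = 0.3* | 0.1 / 0.3 / 0.5 | 7.7 / 13.2 / 18.2% | 7.7 / 12.4 / 17.6% |

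With ICC zero the pooled test is valid (4.3–4.6%). The error therefore runs in either direction: conservative when counts are balanced and the paper effect is shared, liberal when open reports pile up on few papers. Adding a paper-by-process component (ICC 0.2) lifts the balanced case to about 10%.

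**Pooling when volunteering follows the paper effect.** If the open rate is multiplied by exp(m) per SD of the paper effect, the open side is shifted by m × √ICC in units of the score SD. For m = 0.3 and ICC 0.1 this is 0.095 (simulated 0.094). For m = 0.5 and ICC 0.5 it is 0.354 (simulated 0.353). False-positive rates:
- ICC 0.22, Poisson counts: 8.5%, 17% and 32% at m = 0.1, 0.2 and 0.3.
- ICC 0.22, m = 0.5, skewed counts: 67%.
- ICC 0.05, m = 0.5: 23%.
- ICC 0.1 to 0.5, m = 0.3 to 0.5: 18% to 97%.

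**Paper-level signed-rank test.** In the 3000-run settings, with and without selection, it rejected 4.2–5.8% of the time, and under selection its mean difference was about zero.

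**Repeat reviewers.** If 60 open reviewers of uneven activity each carry their own effect (SD 0.35 against a residual SD of 0.57), the pooled test rejects 22–25% and the signed-rank test 17–20%. With 150 equally active reviewers the figures are 7.7% and 5.5%. Pairing by paper does not deal with this.

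**The case against.** A reader might infer that the plan commits to pooling reports as independent samples and that its p-values are therefore wrong. The documents do not support that. A signed-rank test on paper means is non-parametric and satisfies the sentence as written, so the defect is under-specification. No test is named, so none can be shown to be wrong. No confidence intervals are planned, so none can be faulted. Even under pooling, the direction of the error is not fixed.

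A reader might also infer that every paper has several reports of both kinds. Only the standard side is assured of at least two.

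The mechanisms behind the largest figures are assumptions. The instrument scores the report, not the manuscript, and no section says that papers drawing better reports attract more volunteers. Nor is it documented that open reviewers post on several papers; the protocol merely permits it. With Poisson counts and no selection, pooling does no visible harm.

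Finally, this is an observational feasibility study with no stated power or significance level, which lowers the stakes.

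All of this stands, and it limits the strength of the conclusion. It does not close the gap: report quality is the named main outcome, and the sentence leaves open a choice that can change the answer. The appended STROBE checklist refers statistical methods to pages of a manuscript that is not among the documents, so it does not fill the gap either.

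**Conclusion.** The concern holds as a gap in specification. The pairing is built into the design and is not used in the stated analysis, and the natural report-level reading can confuse paper mix with report quality.

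For 170 papers, a mean of one open report and ICC 0.05–0.22, pooled type I error is about 5% with Poisson counts, 7–14% with skewed counts near ICC 0.22 (about 5–6% with mild skew at ICC 0.05–0.10), and roughly 9–70% under selective volunteering. The paper-level signed-rank test stays near 5% in these settings, but not when a few reviewers supply many open reports. ICCs, open counts, selection strength and reviewer activity are all assumed, so these figures show what could happen and do not forecast this study.

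Severity: should fix. It would rank higher in a confirmatory trial with a stated significance level and power.

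**What to change.** Replace the sentence on comparing report quality in Data management and analysis with:

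> The main comparison is the within-paper difference in mean review quality score (open minus standard), in papers with at least one report of each type, tested with a Wilcoxon signed-rank test and reported as a Hodges-Lehmann estimate with 95% CI. A mixed model on report scores with process as fixed effect and random effects for paper and reviewer is a sensitivity analysis that allows for reviewers who report on several papers. Papers without an open report are counted and described.

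This keeps the non-parametric approach and needs no new data: open reviewers must sign, and handling editors choose the standard referees. The cost is a few lines of text and little programming.

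There are three limits. Inference is restricted to papers with both report types, perhaps 51 to 107 of 170 under the counts above. Each paper counts equally however many reports it has. The mixed model's behaviour was not simulated here, which is one reason to keep it as a sensitivity analysis; a scorer effect could be added, since several assistant editors score.

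The research checklist refers to an existing manuscript. If the scores have already been analysed, the paired result should be reported and labelled as specified afterwards.
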